## Abstract

Background. A Cochrane review found that there is insufficient evidence to determine the effectiveness of acupressure for pain relief. One of the problems detected is the methodological variability reported. Objective. To assess the impact of the application of acupressure on obstetric and neonatal outcomes of labor, pain experience, and mother’s satisfaction with the experience. Method. Design of a protocol to carry out a two-arm multicenter single-blinded randomized controlled trial. Intervention (pressure on LI4 of the left hand, B6 of the left leg, GB21 of the left shoulder, and then the same sequence on the right side) and placebo (application of the technique on points not identified by acupuncture as key points) will be performed by a single researcher. Results. The recruitment began in April 2021 and, to date, there has been the participation of 40 women, divided into 17 included in the experimental group and 23 in the control. Communication of future results will be made in accordance with the CONSORT checklist. Conclusions. The designed protocol could methodologically improve some aspects of previous studies while maintaining adequate statistical power. The effectiveness of acupressure for one or more outcomes proposed (time and pain in labor) could support the inclusion of a new therapeutic tool in the clinical practice of midwives that would allow them to assist pregnant women, improving their experience both physically and psycho-emotionally

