## 2. Objectives and Hypothesis

The general objective is to assess the impact of the application of acupressure on obstetric and neonatal outcomes of labor. To achieve the general objective, four specific objectives have been established, each based on the verification or refutation of a specific hypothesis.

Objective 1: To analyze the possible statistical association between the use of acupressure and the times of cervical dilation and fetal delivery.

Null hypothesis: The dilation time and the expulsive time in the women who receive the intervention is the same as those of the women in the control group.Alternative hypothesis: The time of dilation and the time of expulsion in the women who receive the intervention is not the same as those in the women in the control group.

Objective 2: To compare the pain perceived by pregnant women in relation to the use of the acupressure technique.

Null hypothesis: The pain experienced by women receiving the intervention is the same as that experienced by women in the control group.Alternative hypothesis: The pain experienced by women receiving the intervention is not the same as that experienced by women in the control group.

Objective 3: To study the relationship between the use of acupressure and maternal satisfaction regarding the childbirth experience.

Null hypothesis: The satisfaction experienced about the birth process in women receiving the intervention is the same as that in women in the control group.Alternative hypothesis: The satisfaction experienced about the birth process in women who receive the intervention is not the same as that in women in the control group.

Objective 4: Assess the safety of the intervention through fetal and neonatal outcomes.

Null hypothesis: The fetal and neonatal results of the pregnant women belonging to the intervention group are the same as those in the pregnant women of the control group.Alternative hypothesis: The fetal and neonatal results of the pregnant women who belong to the intervention group are not the same as those in the pregnant women of the control group.

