### 3.3. Sampling and Sample Size

The sampling process will be conducted using an intentional or convenience sampling approach, wherein all pregnant women who meet the inclusion criteria and are under the care of the project’s principal investigator will be included until the predetermined sample size is reached. This meticulous approach aims to encompass a diverse range of participants, thereby enhancing the generalizability of the study findings.

The calculation was based on the results obtained in a pilot study (unpublished data) with 17 and 23 women in the intervention and control groups, respectively, using the Gpower 3.1.9.4 software. Different calculations were carried out based on the means and standard deviations obtained in the times of the active, passive, and expulsive phases, as well as on the VAS scale (Likert 1–10 points) used to measure pain. From the different calculations carried out, the one that determined the largest sample size (difference of means in time of expulsive phase) was selected with the intention of having sufficient statistical power for all the analyses proposed.

The means and standard deviation obtained for the expulsive phase time (second stage of parturition, which starts at full dilation and continues until birth) in a pilot study were 46 ± 39 min for the intervention group and 65 ± 47 min for the control group. The number of women per group was calculated to determine a difference in the means of independent groups with alpha = 0.05 (type I error), power (1-beta) = 0.8, and allocation n1/n2 ratio = 1, obtaining a total of 166 women (83 in each group) [23].

Recruitment. The selection of participants for this study will adhere to specific criteria outlined as follows:

Inclusion criteria: The study will include pregnant women who meet the following requirements: Women with induced, accelerated, or spontaneous labor, both primiparous and multiparous, are included.Women who are 18 years of age or older and in the term of their pregnancy (37–42 weeks).Single gestation (not multiple pregnancies).Absence of associated pathologies or medical conditions.Proficient communication skills in the Spanish language.

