The purpose behind administering pressure to different points using fingers in the control group is to eliminate any potential placebo effect associated with “manipulation using a therapeutic instrument”. It is important to note that none of the points pressed in either the intervention group or the control group possess an anatomical location that can induce significant physiological changes when pressure is applied, such as pressing the carotid artery. This precautionary measure ensures the safety of the study participants, minimizing any adverse effects resulting from the applied pressure on the women. Thus, the inclusion of these additional control points not only serves to rule out placebo effects, but also guarantees the well-being and welfare of the participants by preventing any unintended consequences arising from the pressure applied during the study.

Outcomes. Variables will be measured in order to assess the efficacy and safety of the intervention:-Effectiveness of the use of acupressure on labor times in minutes (time of cervical dilatation and time of fetal expulsion according to the recommendations of the World Health Organization).-Effectiveness of the use of acupressure on women’s perceived pain by recording values on the VAS scale and the need for pharmacological analgesic methods. A Visual Analogue Scale (VAS) is a pain rating scale that was first used in 1921 by Hayes and Patterson. The pain VAS is a one-dimensional measure of pain intensity that is used to record the progression of patients’ pain or to compare the severity of pain between patients with similar conditions. The patient must rate their perceived pain on a scale of 0 (no pain) to 10 (the most severe pain imaginable) [1,4,13,14,15,17,19,24,25,26].-Impact of the use of acupressure on maternal satisfaction expressed about the childbirth experience (using the validated satisfaction scale Mackey Satisfaction Childbirth Rating Scale—MSCRS) [8].-Impact of the use of acupressure on neonatal outcomes (Apgar test at 1/5/10 min and arterial blood gases at birth).

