For the comparison of means between dichotomous variables, the Student t-test and ANOVA test will be performed in the case of dichotomous or polytomous variables, respectively, as long as the parametric criteria are met (normality evaluated using the Kolmogorov–Smirnov test and homoscedasticity evaluated with the Levene test). If the parametric criteria are not met, non-parametric tests will be performed (Wilcoxon test and Kruskal–Wallis test, respectively). For the Student t-test analysis, Cohen’s d will be used as a measure of the effect size. 

For regression analysis, the Pearson correlation coefficient will be used. In the case of non-normal distributions, Spearman correlation test will be used. Statistical significance at 5% will be established for all tests.

Ethical aspects. The present study preserves the well-being of the subject above the interests of science or society and the ethical considerations that support it, as part of the compliance with current international and national regulations for health research studies with human beings, as well as that referring to the protection of personal data and clinical information derived from it. Under these premises, this protocol has been approved by the Regional Ethics Committee (committee code 4928, project code: AcuP, approval date 24 February 2021, record number 319).

Data collection notebooks will be handled in which only identification codes will appear that will correspond to the personal data in other guarded records. Similarly, electronic database-type records will be designed disaggregated to avoid identification of patients. An Informed Consent document has been prepared. The intervention does not require invasive tests or manipulation of biological samples beyond those implemented in routine clinical practice.

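### No primary outcome is named and every test runs at an unadjusted 5%, while the Abstract lets any one time or pain outcome support adoption: error rate about 11–18.5% two-sided, about 6–10% in favour of acupressure

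*Protocol article*

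**What the plan says.** - **Hypotheses.** Section 2 sets four specific objectives, each with its own null hypothesis and none ranked above the others. The alternatives are non-directional; for Objective 1: "The time of dilation and the time of expulsion in the women who receive the intervention is not the same".
- **Outcomes.** The Outcomes paragraph of section 3.3 lists two labor times ("time of cervical dilatation and time of fetal expulsion according to the recommendations of the World Health Organization"), two pain measures (VAS and need for pharmacological analgesia), maternal satisfaction (MSCRS), and neonatal results (Apgar at three times, arterial blood gases). None is called primary. The only primary objective mentioned, in the Discussion, is that of the protocol itself: to introduce the intervention.
- **Error rate.** The Data analysis paragraph of section 3.3 states "Statistical significance at 5% will be established for all tests". It gives no adjustment and no order of testing.
- **From result to practice.** The Abstract says: "The effectiveness of acupressure for one or more outcomes proposed (time and pain in labor) could support the inclusion of a new therapeutic tool". Section 6 instead makes support conditional on effectiveness in the outcomes set out in the hypotheses, without saying that one is enough.
- **Sample size.** Section 3.3 reports calculations for the active, passive and expulsive phase times and for VAS. It takes the largest result, that for expulsive time, "with the intention of having sufficient statistical power for all the analyses proposed".

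**The concern.** Taken together, these statements describe a trial in which several outcomes have equal standing, each is tested at 5%, and a positive result on any one time or pain outcome can be carried into practice. Under such a rule the error rate of the overall conclusion is not the 5% used for sizing. With no primary outcome fixed, the headline result can also be chosen after the data are seen.

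The power statement has a related problem. It extends the expulsive-time calculation to analyses that were never calculated.

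**Working it through.** **1. The plan's own sample size.** Inputs from section 3.3: "46 ± 39 min for the intervention group and 65 ± 47 min for the control group", with "alpha = 0.05 (type I error), power (1-beta) = 0.8, and allocation n1/n2 ratio = 1".

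- Pooled SD = √((39² + 47²)/2) = √1865 = 43.19 min.
- Difference = 65 − 46 = 19 min, so d = 19/43.19 = 0.440.
- Two-sample t-test with the noncentral t distribution, two-sided 5%: 83 per group, 166 in total, power 0.804. This matches the stated figure.
- A one-sided test would need 65 per group, so the stated size is two-sided, in line with the non-directional hypotheses.

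The sample size is therefore correct for expulsive time taken alone at 5%.

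**2. The family of tests.** The Abstract limits its statement to time and pain. The Outcomes paragraph gives four such outcomes: dilation time, expulsive time, VAS, and need for analgesia.

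**3. Chance of at least one false positive among the four, if acupressure has no effect on any of them.**

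- Independent tests, two-sided: 1 − 0.95⁴ = 0.185.
- Independent tests, only in favour of acupressure: 1 − 0.975⁴ = 0.096, against 0.025 for one test.
- Correlated tests: simulation of four equally correlated normal test statistics, 1,000,000 draws. The correlations are assumed, because the document gives none.

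| Assumed correlation | Two-sided | In favour of acupressure only |
|---|---|---|
| 0 (formula) | 18.5% | 9.6% |
| 0.2 | 18.0% | 9.1% |
| 0.3 | 17.4% | 8.7% |
| 0.4 | 16.6% | 8.3% |
| 0.5 | 15.6% | 7.8% |
| 0.7 | 13.1% | 6.5% |
| 0.8 | 11.4% | 5.7% |

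**4. Coverage of the power statement.** Calculated: phase times and VAS. Not calculated: analgesic need (part of the pain outcome), MSCRS (Objective 3), and neonatal outcomes (Objective 4).

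**5. Effect of possible remedies on power, at d = 0.440.**

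- One primary outcome, expulsive time, at 5%: 166 women and power 0.80 stand, and the main conclusion is held at 5%.
- Four equal outcomes with Bonferroni: 0.05/4 = 0.0125 each. Power at 83 per group falls to 0.62, and 80% power would need 117 per group (234 in total).

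**The case against.** The strongest reply is that a hierarchy of outcomes and the handling of multiplicity are commonly left to an analysis plan, which is not shown here. That would answer a mere silence. It does not answer this text, which fixes 5% for every test; a later hierarchy or adjustment would have to depart from it.

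Other objections stand and limit the point:

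- **Direction.** The two-sided figure includes results in which acupressure looks worse, and these cannot support adopting it. For a false claim of benefit, the 6% to 10% column is the relevant one.
- **Strength of the wording.** A reader might infer that one significant result is enough to recommend acupressure. The Abstract says only that it could support inclusion, section 6 can be read as asking for the outcomes together, and the Discussion makes incorporation into the health system conditional on demonstrated safety. The documents show an unsettled criterion, not a formal any-one-wins rule.
- **Number of tests.** A reader might count 13 comparisons by adding satisfaction, three Apgar scores and five blood-gas values, and obtain 1 − 0.95¹³ = 49%. The Abstract's statement does not reach those outcomes. The five blood-gas values come from reference ranges listed under independent variables, not from five stated tests. Neonatal outcomes are the safety objective, so a chance finding there is not evidence of effectiveness.
- **Power.** It would be unfair to say that only expulsive time was considered. The other phase times and VAS were calculated and needed fewer women. The gap is confined to the outcomes listed in step 4 of the working.

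**Conclusion.** The point holds in this limited form. The protocol names no primary outcome, applies an unadjusted 5% throughout, and describes the route from result to practice in two ways that do not agree.

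For the four time and pain outcomes, the chance of at least one false positive is 18.5% under independence and about 11% to 18% for correlations of 0.8 to 0.2. In favour of acupressure only, it is about 6% to 10%, against 2.5% for a single test. These figures assume that there is no effect on any of the four, and that the test statistics are roughly normal and equally correlated; the correlations are assumptions. Under every value tried, the rate exceeds that of a single test.

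The claim of power for all analyses is unsupported for analgesic need, satisfaction and neonatal outcomes. The figure of 166 is not in error.

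**What to change.** 1. Name expulsive-phase time, the outcome that sets the 166, as the single primary outcome at two-sided 5%.
2. State whether the 40 pilot women count toward the 166. The pilot had 17 and 23 women, and section 4 reports the same split among women already recruited. The document does not say that they are the same women. If they are, the primary outcome would be named after their expulsive-phase data had been seen, and this should be disclosed.
3. Base the conclusion on effectiveness on that outcome, and bring the Abstract and section 6 into line with it.
4. Make dilation time, VAS, analgesic need and MSCRS secondary, either with Holm adjustment or clearly labelled as supportive. Amend the 5% sentence to match.
5. Report neonatal outcomes as safety estimates with 95% confidence intervals, and reword Objective 4 accordingly, since it is now framed as a hypothesis test.
6. Limit the power statement to the phase times and VAS.

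**Cost.** No more women are needed, and power for the primary outcome stays at 0.80. The change is more than wording, however. With Holm over four secondary outcomes the first step is at 0.05/4 = 0.0125, where power for an effect of the size used in planning is about 0.62.

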## 4. Results

The recruitment and inclusion of women in the study began in April 2021 and, to date, there has been the participation of 40 women, divided into 17 included in the experimental group and 23 in the control. Among them, 95% of the women were treated in a private hospital. They are Spanish women (so far only one woman of Chinese, one of Moroccan, and one of Portuguese nationality have been treated), around 33 years of age, married, with higher education, gestation at term and without complications, with an estimated fetal weight around 3330 kg and with fear of childbirth whose stated reasons were: pain (35%), ignorance (20%), epidural, completion of labor, and loss of control, with 2.5% each. 

To communicate the results, the CONSORT checklist [27] and its flowchart will be used, in order to use a validated instrument whose objective is transparent and free (or minimized) communication of methodological biases.

## 5. Discussion

The primary objective of this study’s protocol is to introduce a novel acupressure intervention, incorporating points that have been extensively studied in the scientific literature and have demonstrated their effectiveness. However, certain points located on the back were deemed impractical due to the supine position in which women typically find themselves during childbirth. Consequently, these points were excluded from the intervention. Conversely, we have identified points from Dávila’s doctoral thesis that have not been previously documented [21]. The strategic positioning of these points enables a more practical and feasible intervention approach. 

Based on the findings, it is anticipated that the meticulously chosen set of points, previously unexplored, will provide a prompt and effective intervention. We expect this intervention to yield improved perinatal outcomes while minimizing discomfort for the mother. By utilizing these previously unexplored points, we aim to optimize the intervention’s efficacy and enhance the overall childbirth experience for women. Therefore, the midwife should position the woman in the standard childbirth posture and can proceed with the intervention, as easy access to the proposed points is ensured in this position. This is crucial from an ergonomic perspective, benefiting both the pregnant woman and the midwife.

The outcomes derived from the implementation of this protocol possess the potential to generate significant and applicable insights for clinical practice, thereby enhancing the overall childbirth experience by reducing pain perception and duration. Consequently, such improvements would directly contribute to heightened satisfaction among women undergoing this crucial life event. Furthermore, if the safety of the intervention for both mothers and infants is demonstrated, its incorporation into the healthcare system of our country would carry substantial weight as a valuable tool for future implementation.

Nevertheless, it is important to acknowledge certain limitations that may arise in relation to the sample size. The current study is based on a small, unpublished pilot study that was organized ad hoc to collect data for the development of this protocol. However, we firmly believe that our meticulous approach will yield more robust scientific evidence compared with previous studies that lacked explicit mention of sample size calculations [14,28] or studies that briefly referenced sample size calculations without providing specific details [1,17,26,29,30,31].

It is noteworthy to highlight that our sample size aligns closely with those observed in other studies published in high-impact nursing journals, reinforcing the methodological robustness of our research [23]. Lastly, we consider the design of a multicenter study with a single researcher responsible for administering the intervention to be a methodological triumph. This approach ensures a greater diversity within the sample population, mitigating potential variations in clinical practices and, to some extent, bolstering external validity.

## 6. Conclusions

If the results of this study confirm the effectiveness of acupressure in achieving the proposed outcomes outlined in the research hypotheses, it would provide substantial support for the integration of this therapeutic modality into the clinical practice of midwives. The inclusion of acupressure as a viable tool would empower midwives to offer comprehensive care to pregnant women, enhancing their overall experience not only on a physical level, but also in terms of their psycho-emotional well-being.

By incorporating acupressure as a part of their practice, midwives would be equipped with an additional evidence-based intervention to address various aspects of pregnancy, labor, and childbirth. This holistic approach to care has the potential to optimize maternal comfort, promote a sense of control and empowerment, and foster positive emotional experiences during this transformative journey.

Furthermore, the integration of acupressure into midwifery practice aligns with the growing recognition of the importance of complementary and alternative therapies in maternity care. It would provide midwives with a valuable tool that complements their existing knowledge and skills, enhancing their ability to provide personalized and holistic care to pregnant women.

Ultimately, the successful implementation of acupressure as a therapeutic intervention within midwifery practice has the potential to positively impact not only the physical well-being of pregnant women, but also their overall satisfaction and emotional connection to the childbirth process. By recognizing and embracing the potential benefits of acupressure, midwives can contribute to a more positive and empowering childbirth experience for women, promoting their overall health and well-being.

